### **Interaction with other medications and other forms of interaction**

Based on the information provided in the Summary of Product Characteristics for *Metforal* 850 mg, simultaneous use is not recommended with:

- Alcohol. Acute alcohol intoxication is associated with an increased risk of lactic acidosis, in particular: at fasting state or inadequate dietary intake; liver failure. Alcohol or ethyl alcohol containing medications should be avoided.
- Contrast medicines containing iodine. Administration of intravascular iodine contrast agents may lead to renal failure, which results in accumulation of metformin and increased risk of lactic acidosis. Metformin should be discontinued prior to the intended examination and should

be restarted at least 48 hours after the examination and re-evaluation of renal function.

### **Use of other medications/substances during the trial**

For safety reasons participants during the study will be asked:

1. To do not use alcohol and alcohol containing medicines that increase the risk of lactic acidosis;
2. To do not use glucocorticoids (systemic and local), sympathomimetics and diuretics with internal hyperglycaemic activity;
3. To do not use angiotensin-converting enzyme (ACE) inhibitors that may lower blood glucose levels;
4. To do not use medicines transported by organic cationic transport molecules-2 (OCT2);
5. Avoid intravascular administration of iodine-containing contrast agents that may cause renal insufficiency and accumulation of metformin hydrochloride and increase the risk of lactic acidosis. If necessary, metformin will be discontinued 48 hours before the intended examination;
6. Inform the investigator about the use of any additional medicines, in order to objectively evaluate adverse reactions and study results.

In cases where the administration of metformin will harm the health status of the participant or confound the effectivity of other indispensable medications, the use of metformin and the participation of the person in the study will be discontinued. Participation in the study will be discontinued even if the participant used undesirable medications (antibiotics, probiotics) during the study, which may affect the study results. Participants will be asked to inform the investigator about the use of other drugs during regular visits and record them in the questionnaire on side effects.

### **Contraindications**

1. Hypersensitivity to the active substance or to any of the excipients in medication (Hypromellose, Povidone K 25, Magnesium Stearate (Ph. Eur.), Hypromellose, Macrogol 6000, Titanium Dioxide (E 171)).
2. Diabetic ketoacidosis, diabetic trauma.
3. Renal impairment (creatinine clearance <60 ml / min).
4. Acute conditions with potentially impaired kidney function, such as
  - a. Dehydration
  - b. severe infection
  - c. shock.
5. Administration of intravascular iodine contrast agents.
6. Acute or chronic disease that can cause tissue hypoxia, such as

- a. heart or respiratory failure,
- b. recent myocardial infarction
- c. shock.

7. Hepatic insufficiency, acute alcohol poisoning, alcoholism.

### **Contraception requirements**

Since metformin is characterized as an antidiabetic agent with unlikely teratogenicity / fetotoxicity in early pregnancy there are no contraceptive requirements for men who have partners with reproductive potential in the study.

Women of childbearing potential must initiate or continue to use the appropriate contraceptive method:

1. Combined (progestogen and estrogen-containing) hormonal contraception;
2. Progestogen hormonal contraception;
3. Intrauterine contraceptive device;
4. Hormone releasing intrauterine contraceptive device;
5. Partner with vasectomy;
6. Complete abstinence;
7. Barrier methods (male or female condom with or without spermicide).

There is no evidence of reduced contraceptive efficacy in metformin users in case of hormonal contraception. The appropriate contraceptive method should be followed throughout the study period and continued for at least 3 days after the last dose of metformin (until the product is released from the body). During the verification period of the study a pregnancy test (beta HCG) will be performed for women with reproductive potential. Additional pregnancy tests are not planned during the study.

### **FOLLOW-UP**

The follow-up period will be 13 days in total, including three days after the last intake of investigational drug in order to record any possible adverse events arose after the active period of the trial and data collection.

### **DATA MANAGEMENT AND STATISTICAL ANALYSIS**

#### ***Data storage and data protection***

The information provided by the participant remains confidential and will not be disclosed without the consent of the participant. The sponsor in cooperation with the LGDB ensures the storage and protection of data in accordance with Latvian legislation (Personal Data Processing Law, into force from 05.07.2018.) Data acquisition, processing, verification and reporting will be carried out by experienced scientific LBMC staff. Access to data will be provided to a limited number of individuals designated by the sponsor and responsible investigator. Data collected in a printed form (questionnaires, diet diary, informed consent form) will be copied and stored for the security reasons in the LGDB premises ensuring

restricted access. Electronic data will be assigned with an authorized approach and will be duplicated on an external data storage device.

The case report form will not be used during the study. Each participant in the study will have a personal data set that will consist of summarized primary documents (general questionnaire, questionnaires on side effects, LGDB questionnaire, diet diary, results of biochemical analysis, reasons for exclusion) and will be stored in printed form. Primary data will be analyzed with specific statistical data processing programs, according to the objectives and tasks of the study. The personal data collected during the study will be stored for 3 years after the end of the study.

The biological material and phenotypic data collected in LGDB during the study will be used only for research purpose. The use of data will be managed in accordance with the restrictions specified in the informed consent form.

For security reasons, the data will be encoded with the code approved by the State Data Inspection and assigned by LGDB. Participant's personal identification data will be stored in the LGDB without access to third parties, in accordance with the Regulations of the Cabinet of Ministers of the Republic of Latvia.

The information about the participant's genotype will be entered into the LGDB and transferred to the The State Genome Registry, as required by Latvian legislation. Compensation for moral damage will be provided if sensitive data obtained during the study will be at the disposal of a third party (in accordance with the Latvian legislation, on a case-by-case basis).

### **Data availability to authorized persons**

The sponsor and investigator will allow any direct monitoring, audit and regulatory inspection of the clinical trial ensuring an access to the primary documentation and associated data. The procedures mentioned above will be conducted in accordance to Regulations of the Cabinet of Ministers of the Republic of Latvia preserving the confidentiality of the participants in the study. By signing the informed consent participants allow their data to be accessed by persons managing the monitoring, audit and regulatory inspections.

### **Methodology for data statistical analysis**

Most of the data within the study will be obtained by massive parallel sequencing techniques, therefore, data pre-processing and specific preparation for statistical analysis is needed (e.g., removing low quality data or data that do not correspond to statistical standards). Data analysis will be performed using such softwares as mothur v.1.39.1, R, RStudio, Galaxy and others. The applied methodology for data statistical analysis may be changed according to offered possibilities, and within the study, the used approaches will be updated to ensure usage of the most recent, best quality, and suitable software, tools, tests, and their versions.

For the gut microbiome data, the sample inner (alpha) diversity and significance of its changes will be calculated (by Shannon index, t-test), as well as performed evaluation of inter-

sample (beta) diversity (principal coordinate analysis (PCoA, R, “vegan”). The statistically significant changes within every taxonomic level will be calculated (statistical tests: t-test, F-test, GLM, regression analysis; R „metagenomeSeq”, „edgeR”, „limma”, „lme4”, „lmerTest”, „multcomp”, „rgl”, etc.).

The data on methylation and RNA expression profiles will be used to determine genomic regions and their associated pathways with significantly altered DNA methylation or RNA expression levels (statistical tests: t-test, F-test, GLM, regression analysis; R „edgeR”, „DESeq2”, „asmn”, „sva”, „limma”, „lumi”, „wateRmelon”, „TCGAMethylation450k”, etc.).

Biochemical, haematological, and anthropometric characteristics will be used as covariates in the performed statistical analyses.

After collection of all data, the following associations will be assessed:

- Between abundance of specific taxonomic groups and severity of observed side effects (chi-squared test);
- Between changes in DNA methylation profile and severity of observed side effects (ANOVA);
- Between abundance of specific taxonomic units and changes in DNA methylation profile (ANOVA);
- Between pharmacokinetic characteristics and abundance of specific taxonomic groups, changes in DNA methylation profile (ANOVA).

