### **Study group**

The study will enroll 50 healthy volunteers of European descent (both sexes) at 18-64 years of age, meeting predefined inclusion/exclusion criteria. Recruitment of the healthy volunteers and further collection of biological samples will be carried out in cooperation with the Genome Database of the Latvian Population (LGDB). Only healthy participants will be involved in the study to avoid potential effect of contributing factors such as the use of other antidiabetic drugs or antibiotics, which may have a systemic effect on microbial composition and epigenetic gene regulation causing biased results. The pre-selected age range of the participants in the study (18-64 years) is defined based on the need for homogeneous microbial compositions among individuals [Claesson et al. 2011; Zapata and Quagliarello 2015]. The number of subjects in the study group is defined on the basis of the calculations of the statistical power of the study (at least 80%), taking into account the potential fluctuations within the size of the study group ( $\approx 2\%$ ), when subjects discontinue the participation in the study for non-research reasons. The confidence level used is  $\alpha = 0.05$ .

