#### Secondary parameters related to efficacy:

1. Association between specific composition of gut microbiome and the severity of the side effects (hi squared value, p-value);
2. The association between DNA methylation at specific loci, gene expression profile with severity of side effects (hi squared value, p-value);
3. The association of the composition of gut microbiome with altered DNA methylation or transcriptome profiles (hi squared value, p-value).
4. Association between pharmacokinetic parameters and specific taxonomic units, changes in DNA methylation profiles and transcriptome profiles (p-value).

The metagenome analysis will provide information on the effect of metformin on the microbial gut, its functions, and the role of microbial in metformin tolerance. The microbiological analysis will be carried out in the specimens of the feces using the methods described above. The effect of metformin on the intestinal microbial will be evidenced by the altered microbial composition and function - a statistically significant change in the number of taxonomic units, genes, proportions, identified metabolites and their concentrations.

Metagenomic analysis will provide information about the metformin-induced alterations in gut microbiome and its role in the tolerance of metformin. The metagenomic analysis will be performed by using stool samples and the effect of metformin will be evaluated by altered composition and function of gut microbiome - significantly changed number of taxonomic units, genes, proportions, metabolites and their concentrations.

Venous blood samples will be further used for DNA methylation and RNA expression analysis. The effect of metformin on the epigenetic regulation will be confirmed by statistically significant alterations in the DNA methylation and transcriptome profiles after the administration of metformin, and the functionality of these alterations will be confirmed based

on the correlation between the DNA methylation profiles and the RNA expression intensity at specific loci.

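### Two secondary associations carry chi-squared in one section and ANOVA in another, and taxa versus severity is chi-squared in both, which needs undefined abundance classes and ignores the order of severity

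*Protocol*

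**What the plan says.** Secondary parameters related to efficacy lists four associations, each followed by the statistic to be reported. Item 1 (microbiome and severity) has a chi-squared value. Item 2 reads "The association between DNA methylation at specific loci, gene expression profile with severity of side effects (hi squared value, p-value". Item 3 reads "The association of the composition of gut microbiome with altered DNA methylation or transcriptome profiles (hi squared value, p-value". Item 4 (pharmacokinetics) has a p-value and no named test.

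The closing list of Methodology for data statistical analysis has four matching lines:
- taxa and severity: "Between abundance of specific taxonomic groups and severity of observed side effects (chi-squared test";
- methylation and severity: "Between changes in DNA methylation profile and severity of observed side effects (ANOVA";
- taxa and methylation: "Between abundance of specific taxonomic units and changes in DNA methylation profile (ANOVA";
- pharmacokinetics with taxa or methylation: ANOVA.

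AE classification by severity defines the ordered grades mild, moderate and severe. Primary parameters for efficacy measurements treats taxa as proportions and methylation as Beta values, both continuous. On size, Study group states: "The study will enroll 50 healthy volunteers of European descent (both sexes) at 18-64 years of age".

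**The concern.** For two associations the same question has two tests in one document. One of these, methylation versus severity, is also secondary endpoint 2 in Endpoints of the study. An analyst could follow either section and claim to be following the protocol, and the two tests can disagree on the same data.

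For taxa versus severity (secondary endpoint 3) the sections agree, but on a poorly suited test. A chi-squared test of association works on counts in a cross-table. Abundance must first be cut into classes, and the protocol gives no rule for the cuts, so the p-value depends on a choice still to be made. The test also treats none, mild, moderate and severe as unordered labels and so discards the dose-like information in the grade. At stake is the chance of detecting a real association in a study of 50 people.

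**Working it through.** **Step 1. Compare the sections.**

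| Association | Secondary parameters | Methodology | Conflict? |
|---|---|---|---|
| Taxa – severity | chi-squared | chi-squared | no |
| Methylation – severity | chi-squared | ANOVA | yes |
| Microbiome – methylation | chi-squared | ANOVA | yes |
| Pharmacokinetics – taxa, methylation | p-value only | ANOVA | no |

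The conflict affects two of the four. Items 2 and 3 also cover gene expression, which the Methodology list does not mention in these pairs, so expression keeps its chi-squared label.

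**Step 2. The plan's own figure.** Study group gives 50 participants, at least 80% power, α = 0.05 and about 2% loss. The loss step is consistent: 50 × 0.98 = 49. The 50 itself cannot be reproduced, because no effect size, endpoint or test is attached to it, and no power is stated for the associations. As a yardstick, the correlation between two continuous variables detectable with 80% power (two-sided) in 49 people, by Fisher's z, is tanh[(1.96 + 0.84)/√(49 − 3)] = tanh(0.413) = 0.39.

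**Step 3. Power for severity, n = 50, α = 0.05.** Assumed, not in the protocol: a bivariate normal latent model, latent correlation 0.4 or 0.5, and the severity mixes shown. Chi-squared uses abundance split at the median. Relative loss = 1 − (power of the test ÷ power of Spearman).

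| Severity mix (%) | Correlation | Spearman | Chi-squared | Loss |
|---|---|---|---|---|
| 60/25/10/5 | 0.4 | 66% | 29% | 1 − 29/66 = 56% |
| 60/25/10/5 | 0.5 | 86% | 48% | 1 − 48/86 = 44% |
| 80/10/7/3 | 0.4 | 52% | 16% | 1 − 16/52 = 69% |
| 80/10/7/3 | 0.5 | 72% | 29% | 1 − 29/72 = 60% |
| 60/40 (two levels) | 0.4 | 60% | 47% | 1 − 47/60 = 22% |
| 60/40 | 0.5 | 81% | 67% | 1 − 67/81 = 17–18% (rounding) |
| 70/30 | 0.4 | 57% | 42% | 1 − 42/57 = 26% |
| 70/30 | 0.5 | 78% | 61% | 1 − 61/78 = 22% |

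The number of classes matters too. With n = 49, severity 50/30/15/5 and correlation 0.45, Spearman has 80% power and chi-squared has 43%, 40% or 35% with two, three or four abundance classes.

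**Step 4. ANOVA of a continuous variable across severity groups.** In the four four-level rows above, ANOVA against Spearman is 51% v 66%, 75% v 86%, 37% v 51% and 56% v 72%. The losses run from 1 − 75/86 = 13% to 1 − 37/51, about 28%.

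**Step 5. Validity of chi-squared.** With a median split of 50 people each row holds 25. Under 60/25/10/5 the expected counts per row are 15, 6.25, 2.5 and 1.25, so half are below 5. With no true association, the test rejected in 3.7% (60/25/10/5) and 2.3% (80/10/7/3) of simulated trials. It is conservative there, and near nominal with two levels.

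**Step 6. Both sides continuous, n = 49, correlation 0.39.** Pearson correlation has 81% power, ANOVA on binned values 55–59%, and chi-squared on binned values 30–38%. The ANOVA figure applies only if one variable is actually cut into groups.

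**The case against.** These are secondary associations in a study that calls itself exploratory, and Methodology for data statistical analysis allows its methods to be updated. That section also lists the F-test, GLM and regression, so ANOVA between two continuous variables may simply mean the F-test of a regression term, which needs no cuts. This last point stands: for those pairs the wording is ambiguous and not demonstrably wrong. The freedom to change methods does not reconcile two sections that already name different tests.

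The four-level severity mixes may also be pessimistic. Potential benefits and risk factors says that participants with moderate or severe side effects stop the drug, and Premature withdrawal of subjects lists such reactions as a reason for withdrawal. Analysed participants could therefore be mostly without side effects or with mild ones, although data from withdrawn people may be used case by case. With two levels there is no ordering to lose, small cells largely disappear and the loss falls to about 18–26%. This stands, and is why both ranges are given.

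A reader might also fault the protocol for not fixing which stool sample enters the severity test, or for giving no false-discovery rule for these families. A statistical analysis plan may hold such detail and is not shown, so neither is part of this point.

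**Conclusion.** The contradiction is certain from the text, for methylation versus severity and for microbiome versus methylation. The poor fit of chi-squared for taxa versus severity is also clear: undefined classes and an ignored order. The size of the loss is conditional. It is about 44–69% of Spearman's power with four severity levels and about 18–26% with two, at n = 50, a median split and latent correlations of 0.4–0.5. The protocol gives neither the severity mix nor the effect size.

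Stronger readings are not supported:
- That neither test fits. ANOVA of methylation change across severity groups is valid; it ignores the order, at a cost of about 13–28%.
- That chi-squared is invalid. It is conservative or near nominal in these settings; the problem is power and the arbitrary cuts.
- That more than half the power is lost in general. One of the four four-level cases and all of the two-level cases fall short of that.
- That all four associations conflict. Taxa versus severity has the same test in both sections, and the pharmacokinetic item has no named test in one of them.

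**What to change.** Make Secondary parameters related to efficacy and Methodology for data statistical analysis name the same test for each association:

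- **Severity with taxa, methylation or expression:** Spearman correlation, or ordinal regression of the severity grade on the unbinned value, in place of chi-squared. If only two or three people have the top grade, ordinal regression is sparse as well, and Spearman is the simpler choice.
- **Both sides continuous** (taxa with methylation, taxa with expression, pharmacokinetics with taxa or methylation): Spearman correlation or linear regression on the unbinned values, in place of chi-squared or grouped ANOVA. If ANOVA was meant as the F-test of a regression term, say so.

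The variables can stay as the Methodology section states them, for example change in methylation. The cost is a small wording change and no new data or samples. Spearman's coefficient already appears in Primary parameters for efficacy measurements, and regression in the Methodology section.

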## **QUALITY ASSURANCE**

The sponsor is responsible for ensuring and controlling the quality of activities carried out and the data obtained within the framework of the study. The collection, transportation, processing and storage of the samples will be performed on the basis of internal standard operation protocols developed by the Sponsor (SOP), which comply with guidelines for good clinical practice and the Regulations of the Cabinet of Ministers of the Republic of Latvia.

Venipuncture will be performed by a certified medical personnel, using single use systems, ensuring full safety for patients and medical personnel, and by excluding contamination errors in the analysis performed. For the purpose of monitoring the quality of the collection of the stool samples and transfer instructions will be issued to the research participants. Storage of stool and blood samples will take place under conditions appropriate to the type of sample (observing sterility, temperature, etc.).

Biochemical and hematological analysis will be performed by E. Gulbis Laboratory certified medical personnel, in accordance with the quality requirements of LVS EN ISO 15189:2007. The analysis of microbiome, DNA and RNA will be carried out by trained personnel of the LBMC, in accordance with the analytical methods protocols developed by

LBMC. The statistical processing of the resulting data will be carried out by qualified LBMC staff on the basis of an internationally accepted methodology, adapted to the design of the study. The sponsor, in cooperation with the LGDB (certified data keeper), provides storage and protection of data in accordance with the Personal Data Processing Law (into force from 05.07.2018.). Access to data related to the progress of the study will be provided to a limited number of persons selected by the Sponsor.

### **Monitoring**

Monitoring will be done by a sponsor-selected person having a prior scientific experience in local and international research projects. Monitoring will be performed before the beginning of the trial, during the trial and at the end of the trial. The purpose of the monitoring is to evaluate the respect of participant rights, the reliability of the reported data and their compliance with the source data, the compliance of the study process with the National legislation of Latvia, the sponsor's internal standard protocol of operations, the study protocol, and Guideline for Good Clinical Practice. Within the framework of the monitoring, the qualification of the research team and available resource, the process of delivery, storage and release of investigational drug will be evaluated. In addition, monitor will verify the time of signing the informed consent, documentation of adverse reactions, filling and storage of all the documentation related to the participant, documentation of any withdrawal. Following the monitoring, the monitor will submit a written and dated report to the sponsor summarizing the monitoring activities and observed discrepancies. The monitor will advise the investigator or his team on further actions if necessary.

